**Methods/Design:**

This pragmatic, prospective controlled trial will enrol 660 wait-listed subjects (220 per study arm) from regional bariatric programs in Alberta and randomly assign them to: 1. an in-person, group-based intervention (9 modules delivered over 10 sessions); 2. a web-based intervention (13 modules); and 3. controls who will receive mailed literature. Subjects will have three months to review the content assigned to them (the intervention period) after which they will immediately enter the weight management clinic. Data will be collected at baseline and every 3 months for 9 months (study end), including: 1. Clinical [5% weight loss responders (primary outcome), absolute and % weight losses, changes in obesity-related comorbidities]; 2. Humanistic (health related quality of life, patient satisfaction, depression, and self-efficacy); and 3. Economic (incremental costs and utilities and cost per change in BMI assessed from the third party health care payor perspective) outcomes. Covariate-adjusted baseline-to-nine-month change-scores will be compared between groups for each outcome using linear regression for continuous outcomes and logistic regression for dichotomous ones.

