## Objectives

The EVOLUTION Trial is designed to:

1. Assess the clinical effectiveness of the WWCM program in reducing weight, improving obesity-related comorbidity and decreasing Adult Clinic attrition rates compared to controls.

2. Determine if the WWCM program improves humanistic outcomes including health-related quality of life, patient satisfaction, self-efficacy and readiness-to-change compared to controls.

3. Determine the incremental cost and cost-effectiveness of the WWCM program.

4. Compare the in-person delivery of WWCM content to online delivery in terms of efficacy and cost-effectiveness.

In aggregate, these objectives will assess the program’s impact on a comprehensive range of outcomes important to patients, providers, and policy-makers. Because the WWCM program is intended to prime patients for success as they receive care in the Adult Clinic, the primary outcomes will be measured prior to attending WWCM modules and then repeated six months after entry into the Adult Clinic.

We hypothesize that both online and in-person delivery of the WWCM intervention will reduce body weight and improve clinical and humanistic outcomes at 9 months compared to the control group. Furthermore, we hypothesize that the in-person version of the intervention will be more effective (as a consequence of greater interpersonal contact) but also more costly than the on-line version. Although we hypothesize that the program will be beneficial, this is by no means certain. It is possible that outcomes in the groups receiving the WWCM intervention will be no better than controls, only marginally better, or improved but not in a cost-effective manner. This underscores the need for rigorous program evaluation to ensure that current program delivery - as well as potential future expansion - is warranted.

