### Data collection and outcome measures

Unless otherwise indicated, data will be collected at baseline, and at 3, 6 and 9-months post-randomization (Additional file 1); the 9-month time point is the one of primary interest (see Figure 1). Study personnel will collect data using standardized case report forms (paper copies will be retained and securely stored) and data transferred on a daily basis to an electronic database using a secure, internet-based portal.

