**Figure 1 F1:**
[figure not shown]
Study overview.

1. **Sociodemographic data (baseline only):** This includes age, sex, race, marital status, household income and employment status.

2. **Obesity-related comorbidities and past medical history:** includes blood pressure taken with a Watch BP® automated monitor (three readings simultaneously in each arm; first reading discarded and the latter two averaged; higher arm average used as the primary endpoint), fasting lipids and glucose, A1c, creatinine, alanine aminotransferase (ALT) smoking status and cardiovascular medications.

3. **Specific obesity-related variables:** weight, height (using a clinic based stadiometer), BMI.

4. **Quality of life and utility measurement:** Validated generic health related quality of life (SF-12 [35] and EQ-5D [30]) instruments will be used. Preference-based utilities will be measured using the EQ-5D.

5. **Satisfaction with medical care:** assessed using two questions from the Patient Satisfaction Questionnaire (PSQ) [31] that will be scored on a 5-point Likert Scale.

6. **Self-efficacy:** Obesity-specific self-efficacy will be measured using the validated Weight Efficacy Life-Style Questionnaire (WEL), a 20-item instrument that assesses self-efficacy across 5 situational factors (negative emotions, availability, social pressure, physical discomfort and positive activities) [32].

7. **Screening for Depression:** the Patient Health Questionnaire (PHQ-8), a validated screening tool for depression, will be used [33].

8. **Readiness-to-Change:** assessed using a a Visual Analogue scale ranging from 0 to 10.

9. **Attrition Rates (at 6 and 9 months only):** attrition rates within the multidisciplinary clinic will be assessed and compared between study arms.

10. **Costing Data:** Costing will adhere to the three-step micro-costing technique of identification, measurement, and valuation of resources. We will determine the overall and per-patient total and incremental costs of the two versions of the WWCM program and the control arm [34,35]. Start-up costs and on-going program delivery costs for each study arm will be tabulated. The cost per patient will be estimated using the current enrolment in the WWCM, as well as best- and worst-case scenarios (minimal and maximum session capacity) [34,35].

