#### Data analysis

Descriptive analyses will be performed and data will be examined graphically and serial changes described. Because these are self-reported data collected every 3 months, we will use a “last-value carried forward” approach to handle missing data as our primary analytic strategy. For example, temporal trends in the SF-12 will be assessed graphically and using analysis of variance (ANOVA) as a test of trends over time. Multivariable, adjusted 9-month changes in continuous measures will be assessed using linear regression in a manner similar to that detailed for the clinical outcome analysis. Patient satisfaction will be categorized as a dichotomous variable [31] and multivariable predictors of deterioration in satisfaction will be determined in serially constructed models.

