#### Sample size considerations

The sample size of 660 subjects has more than adequate power. For example, for a nine month change in SF-36 domains such as physical function, with baseline score of 60, SD 19 [43], a deterioration of 10 points, two-sided alpha=0.05, beta=0.90, and a 10% attrition rate, only 85 total patients would be required. Similarly, for an outcome such as satisfaction, with baseline measures of 70% satisfied with care, a 30% deterioration in satisfaction over 1 year, and otherwise similar power-related assumptions, 136 total patients are required.

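### Objective 2 asks whether the program improves satisfaction, but the satisfaction-specific model counts only deterioration and so answers the objective only in part

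*Protocol article*

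**What the plan says.** The second item under Objectives is directional and comparative: "Determine if the WWCM program improves humanistic outcomes including health-related quality of life, patient satisfaction, self-efficacy and readiness-to-change compared to controls". The hypotheses in the same section also expect better humanistic outcomes than controls at 9 months.

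The abstract (Methods/Design) lists patient satisfaction among the humanistic outcomes and then gives a general rule: "Covariate-adjusted baseline-to-nine-month change-scores will be compared between groups for each outcome using linear regression for continuous outcomes and logistic regression for dichotomous ones".

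Under Humanistic endpoints, Data analysis, satisfaction gets its own treatment. First, "Patient satisfaction will be categorized as a dichotomous variable"; then "multivariable predictors of deterioration in satisfaction will be determined in serially constructed models". That section opens with a general statement covering all humanistic data: "Descriptive analyses will be performed and data will be examined graphically and serial changes described". Its link back to the clinical analysis covers continuous measures only.

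Under Humanistic endpoints, Sample size considerations, the power example for satisfaction is worded as "with baseline measures of 70% satisfied with care, a 30% deterioration in satisfaction over 1 year", giving 136 patients in total.

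Satisfaction is measured by two questionnaire items on a 5-point scale. The general schedule applies to them: "data will be collected at baseline, and at 3, 6 and 9-months post-randomization".

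**The concern.** On a continuous scale, modelling change covers gains and losses together. On a binary variable, deterioration and improvement are different events in different patients. Only those satisfied at baseline can deteriorate, and only those not satisfied can improve. A model whose event is deterioration codes a patient who becomes satisfied the same as one who stays dissatisfied, or leaves both out.

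The objective asks about improvement, while the satisfaction-specific text and the planning example both concern loss. The two humanistic passages agree with each other, so this does not look like a slip in one sentence.

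Satisfaction is a secondary outcome and the primary 5% responder result is unaffected. It can still matter to the trial's conclusion. The clinical sample size section says that a program falling short of the 15% difference would not be worth continued funding unless there were compelling humanistic or cost-effectiveness benefits. Satisfaction is one of the humanistic outcomes that could be cited for that purpose.

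**Working it through.** **Inputs.** From Humanistic endpoints, Sample size considerations: 70% satisfied at baseline; a 30% deterioration; two-sided alpha 0.05; power 0.90 (printed as beta = 0.90); 10% attrition, taken as carried over to satisfaction from the preceding example. From Study design: 220 per arm, 660 in total. From the clinical sample size section: 30% possible loss to follow-up, which leaves 220 × 0.70 = 154 per arm.

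**1. What the planning figure of 136 represents.** Read the 30% as absolute, 70% versus 40%, in two equal groups.

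- Uncorrected: n = [1.96·√(2 × 0.55 × 0.45) + 1.2816·√(0.70 × 0.30 + 0.40 × 0.60)]² / 0.30² = (1.379 + 0.860)² / 0.09 = 55.7, so 56 per arm.
- With continuity correction: n = (55.7/4) × [1 + √(1 + 4/(55.7 × 0.30))]² = 62.2, so 63 per arm.
- With 10% attrition: 63/0.90 = 70 per arm, 140 in total.

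This is within 3% of the stated 136, so the figure is approximately reproduced. The uncorrected version gives 126 in total and does not match. Read as relative (70% to 49%), the corrected number is 123 per arm, 137 after attrition and 274 in total. The stated total therefore fits the absolute reading. Either way, the effect planned for is a fall in satisfaction.

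**2. Who can have the stated event.** On a satisfied/not-satisfied dichotomy, the share who cannot deteriorate is 1 − 0.70 = 0.30.

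- Per arm: 0.30 × 220 = 66.
- Whole trial: 0.30 × 660 = 198.

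**3. What a gain in that group does.** Let Δ be the between-arm difference in the proportion of initially dissatisfied patients who become satisfied, with deterioration equal in both arms. The difference in the proportion satisfied at 9 months is then 0.30 × Δ, and the difference in deterioration is zero. The article gives no conversion rates, so Δ is an assumption:

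| Assumed Δ | Difference in proportion satisfied | Difference in deterioration |
|---|---|---|
| 30 points (e.g. 30% vs 60%) | 9 points | 0 |
| 40 points (e.g. 20% vs 60%) | 12 points | 0 |

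The second row in full, assuming that 10% of satisfied patients deteriorate in every arm:

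- Deterioration: 0.70 × 0.10 = 7% in both arms.
- Satisfied at 9 months, control: 0.70 × 0.90 + 0.30 × 0.20 = 69%.
- Satisfied at 9 months, program: 0.70 × 0.90 + 0.30 × 0.60 = 81%.

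**4. Power of the endpoint that captures gains.** Power = Φ{[d√n − 1.96·√(2p̄(1 − p̄))] / √(p₁(1 − p₁) + p₂(1 − p₂))}, where d is the difference in proportions and p̄ their mean. For 69% versus 81% at n = 220: (0.12 × 14.83 − 1.200)/0.606 = 0.956, so power is 0.83.

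| Control vs program, satisfied at 9 months | 220 per arm | 154 per arm |
|---|---|---|
| 69% vs 81% | 0.83 | 0.68 |
| 70% vs 80% | 0.68 | 0.53 |
| 70% vs 85% | 0.97 | 0.89 |

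In the 69% versus 81% scenario, the deterioration model has no difference to find, while the proportion satisfied shows it with fair power.

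**The case against.** The best defence is the abstract. It names satisfaction as an outcome and promises an adjusted between-group comparison of baseline-to-9-month change for each outcome, by logistic regression where the outcome is dichotomous. That rule has no built-in direction and is close to the fix below. Serial changes are also to be described, and the data exist at four time points. A reader might infer that gains are invisible to the whole plan, or that Objective 2 cannot be answered for satisfaction; the article does not support either reading. What remains is that the abstract does not say what change means for a binary item, and the methods text, where it becomes specific, names deterioration alone.

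A reader might also take the word predictors to mean that the effect of study arm is not estimated. The clinical Data analysis section uses the same word, and its worked example for weight then estimates the independent effect of the program. That inference should not be drawn.

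Nor is a spurious benefit from unequal baseline satisfaction a fair charge. Allocation is randomised with 220 per arm, so imbalance is a matter of chance, and the clinical section adjusts for significant or clinically important between-group differences.

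The chosen direction has a rationale. The background reports that wait-listed patients feel waiting contributes to their decline, and losing less satisfaction than controls would be a real, if partial, benefit. This stands, and it is why the model answers the objective in part.

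Finally, a condensed article may leave the exact event definition and denominator to the full protocol or analysis plan. That excuses missing detail. It does not excuse a named endpoint that points away from the objective.

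**Conclusion.** The mismatch holds, in limited form. The objective is improvement against controls; the only satisfaction-specific model, and the power example beside it, concern deterioration. Gains among patients not satisfied at baseline fall outside that model, which by itself answers Objective 2 only in part.

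The size is about 30% of patients, or 66 of 220 per arm. It rests on two assumptions: that the dichotomy is satisfied versus not satisfied, which is the natural reading though the cut is not given, and that the 70% used for planning is near the true baseline rate. The 9- and 12-point differences depend on assumed conversion rates and show the mechanism only; they do not predict the result. The matter is a secondary outcome and worth correcting because the correction is cheap.

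**What to change.** In Humanistic endpoints, Data analysis, replace the deterioration sentence so that it agrees with Objective 2 and the abstract. The endpoint becomes satisfied at 9 months (yes/no), with the dichotomy already intended, in all randomised patients. Each program arm is compared with control by logistic regression on study arm, with baseline satisfaction as a covariate. Deterioration among those satisfied at baseline stays as a descriptive secondary.

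The satisfaction example under Sample size considerations should then be restated for a difference in the proportion satisfied, saying whether the difference is absolute or relative, because the present figure concerns a 30-point fall.

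The cost is one sentence in the analysis section and one in the planning section. Nothing new is collected: the items are already scheduled at baseline, 3, 6 and 9 months.

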#### Sample size considerations

The sample size of 660 subjects has more than adequate power. For example, for a nine month change in SF-36 domains such as physical function, with baseline score of 60, SD 19 [43], a deterioration of 10 points, two-sided alpha=0.05, beta=0.90, and a 10% attrition rate, only 85 total patients would be required. Similarly, for an outcome such as satisfaction, with baseline measures of 70% satisfied with care, a 30% deterioration in satisfaction over 1 year, and otherwise similar power-related assumptions, 136 total patients are required.

### Economic endpoints

#### Outcomes

The total and incremental cost of WWCM (web-based and in-person) vs. controls (by program and per patient) will be determined and the incremental cost per QALY gained (cost-utility), and cost per incremental difference in BMI (cost-effectiveness) will be calculated.

#### Methods and analyses

A validated economic model of interventions in bariatric patients will be adapted to compare each version of the WWCM program vs. controls while adhering to recommended best practices for conduct of economic evaluation [18,44]. The model will be informed by primary data, including costing data, utility scores (EQ-5D) and changes in BMI in the 3 groups at 9-months. A 9-month time horizon and a public health care payer perspective will be used. No discounting of costs and benefits will be performed in the reference case (given the short time frame). Uncertainty and variability will be explored through sensitivity analysis, including one-way and probabilistic sensitivity analysis to determine if results are modified over a plausible range of model inputs (for example, 95% confidence intervals of differences in EQ-5D, or variability in cost per patient of the WWCM program). If differences in BMI are found between the treatment groups at 9-months, we will perform an exploratory lifetime analysis linking BMI at 9-months to longer term health outcomes (including probability of developing complications such as diabetes, sleep apnea, long-term quality of life, and risk of death) as conducted in our previous work [18,19,44,45].

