## Abstract

**Background:**

In Canada, demand for multidisciplinary bariatric (obesity) care far outstrips capacity. Consequently, prolonged wait times exist and contribute to substantial health impairments.

A supportive, educational intervention (with in-person and web-based versions) designed to enhance the self-management skills of patients wait-listed for multidisciplinary bariatric medical and surgical care has been variably implemented across Alberta, Canada. However, its effectiveness has not been evaluated. Our objectives were: 1. To determine if this program improves clinical and humanistic outcomes and is cost-effective compared to a control intervention; and 2. To compare the effectiveness and cost-effectiveness of in-person group-based versus web-based care. We hypothesize that both the web-based and in-person programs will reduce body weight and improve outcomes compared to the control group. Furthermore, we hypothesize that the in-person version will be more effective but more costly than the web-based version.

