**Discussion:**

Our findings will determine whether this intervention is effective and cost-effective compared to controls and if online or in-person care delivery is preferred. This information will be useful for clinicians, health-service providers and policy makers and should be generalizable to similar publically-funded bariatric care programs.

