**Module three - finding balance: the role of calories in weight management**	Learn about the top 5 ways to lower calories and practice strategies in class.
**Module four - managing hunger and appetite**	Explore the difference between hunger and appetite.
	Practice techniques to manage appetite triggers and social pressures.
**Module five - moving matters – including physical activity in your day**	Explore the benefits and barriers to being more active.
	Receive tips on how to get more physically active.
	Set your own personal activity goals.
**Module six - nutrition: the truth about what works in weight management**	Evaluate what you are eating and learn strategies that can help lower your calories.
	Explore how meal patterns, food choices and portion size affect calorie intake.
	Learn about which foods can help you manage your weight.
**Module seven - nutrition: i know i should eat healthy, but how?**	Leave with tips on how to put your nutrition knowledge into practice.
	Explore the 4 P’s: **P**lan, **P**urchase, **P**repare and **P**ack.
**Module eight- nutrition: eating away from home and during special occasions**	Learn how buffets, parties, vacation and holiday eating can affect calorie intake.
	Leave with strategies to minimize extra calories when eating away from home and during special occasions.
**Module nine - minding stress: effectively reduce and manage the stress in your life (two consecutive sessions)**	Learn about all the different reasons why people eat.
	Learn how to cope with emotional eating.
	Learn how to feel more in control of your eating.

The evidence-based curriculum [10] stresses healthy eating; gives practical tips to increase physical activity; teaches basic behavioural modification techniques such as goal setting and self-monitoring; and includes strategies for dealing with stress and maladaptive eating behaviours such as emotional eating. Each module is 2.5 hours in length and is led by the appropriate content expert(s) from a team of 4 registered nurses (3.2 FTE), 1 Canadian Society for Exercise Physiology (CSEP) specialist, 1 MSc psychologist and 1 registered dietician.

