## Discussion

In summary, EVOLUTION is a pragmatic randomized controlled trial that will determine if an existing intervention, the WWCM program, improves health outcomes in a cost-effective manner. In addition, if effective, the optimal care delivery method (in-person versus online) will be identified.

The population-based nature of the bariatric specialty clinics from which EVOLUTION subjects will be enrolled enhances generalizability because the structure of these clinics is similar to those found in other provinces within Canada. If EVOLUTION demonstrates that the WWCM program is effective and cost-effective, we anticipate that other programs will seek to implement similar interventions. If WWCM program has limited effectiveness or cost-effectiveness, it’s use should be re-evaluated and funding reallocated to other bariatric care initiatives. Thus, no matter the study findings, we feel that they will assist health-service providers and policy makers to better allocate use of finite resources.

EVOLUTION commenced enrolment in March 2013. Recruitment of all 660 subjects is expected by end-2015. Final study results are anticipated in 2016.

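### Objective 4 asks for the cost-effectiveness of in-person versus online delivery, but the economic methods name controls as the comparator and do not carry the head-to-head comparison through

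*Protocol article*

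**What the plan says.** The head-to-head economic question appears twice as an objective. Objective 4 (Objectives) reads "Compare the in-person delivery of WWCM content to online delivery in terms of efficacy and cost-effectiveness", and the second objective in the Abstract (Background) reads "To compare the effectiveness and cost-effectiveness of in-person group-based versus web-based care". The conclusions are worded to match. The Abstract's Discussion says the findings will show "if online or in-person care delivery is preferred", and the main Discussion says that, if the program is effective, "the optimal care delivery method (in-person versus online) will be identified".

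The economic section is framed differently. Under Economic endpoints, Outcomes: "The total and incremental cost of WWCM (web-based and in-person) vs. controls (by program and per patient) will be determined". The same sentence goes on to promise a cost per QALY and a cost per difference in BMI without naming a comparator for those ratios. Under Economic endpoints, Methods and analyses, a validated model "will be adapted to compare each version of the WWCM program vs. controls", informed among other things by "changes in BMI in the 3 groups at 9-months".

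Two other places bear on the point. Statistical analyses and sample size considerations says that later analyses will compare outcomes between the in-person and online interventions. Item 10 (Costing Data) under Data collection and outcome measures plans total and incremental costs for both versions and the control arm, without saying which pairs are compared.

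**The concern.** A payer who can fund one of three mutually exclusive options (mailed literature, web, in-person) needs the incremental comparison along the cost ranking: web against control, then in-person against web if in-person costs more and achieves more. The protocol's own hypothesis is that ordering, with in-person delivery giving the larger benefit at the larger cost. The decisive quantity is then the cost of the extra benefit gained by moving from web to in-person, and the economic section does not state that comparison.

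Both versions could look acceptable against controls while the additional spending on group sessions buys little. Equally, the version with the lower ratio against controls could be preferred although the dearer one is the better buy. In either case a statement about the optimal mode would not follow from the analysis described.

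**Working it through.** **No figure to reproduce.** The protocol states no cost, QALY gain, ratio or willingness-to-pay threshold for this comparison. The check therefore has two parts: question against method, and an illustration with assumed inputs.

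**Question against method**

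| Place in the protocol article | Comparison named |
|---|---|
| Abstract, Background; Objective 4 | in-person v online, cost-effectiveness |
| Abstract, Discussion; Discussion | preferred or optimal mode |
| Economic endpoints, Outcomes: incremental cost | each version v controls |
| Economic endpoints, Outcomes: ratios | no comparator named |
| Economic endpoints, Methods and analyses: model | each version v controls |
| Statistical analyses, opening paragraph | in-person v online, outcomes in general |

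The objective and the stated economic comparator do not match. The only bridging sentence is general and names neither costs nor ratios.

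**Why two ratios against controls do not settle it.** Let Cw, Qw be the cost and QALY increments of web over control, Cp, Qp those of in-person over control, and λ the threshold.

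- Ratios against control: Cw/Qw and Cp/Qp.
- Step ratio, in-person v web: (Cp − Cw)/(Qp − Qw).
- Net monetary benefit (NMB) v control: λQ − C.

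With 0 < Qw < Qp, Cp/Qp is a weighted average of Cw/Qw and the step ratio, with weights Qw/Qp and (Qp − Qw)/Qp. So whenever web has the lower ratio against control, the step ratio is higher than the in-person ratio against control. In-person is worth choosing over web only if the step ratio is below λ. Both ratios against control being below λ does not guarantee that.

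**Illustration.** All increments are assumed, per patient, and so is λ = $50,000 per QALY.

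| Case | Web v control | In-person v control | Web ratio | In-person ratio | Step ratio | NMB web | NMB in-person |
|---|---|---|---|---|---|---|---|
| A | $100, 0.010 | $600, 0.014 | $10,000 | $42,857 | $125,000 | $400 | $100 |
| B | $100, 0.010 | $500, 0.015 | $10,000 | $33,333 | $80,000 | $400 | $250 |
| C | $100, 0.010 | $500, 0.012 | $10,000 | $41,667 | $200,000 | $400 | $100 |
| D | $100, 0.005 | $500, 0.015 | $20,000 | $33,333 | $40,000 | $150 | $250 |

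Case A in full: 100/0.010 = 10,000; 600/0.014 = 42,857; (600 − 100)/(0.014 − 0.010) = 500/0.004 = 125,000. NMB is 50,000 × 0.010 − 100 = 400 for web and 50,000 × 0.014 − 600 = 100 for in-person. Weighted-average check: (0.010 × 10,000 + 0.004 × 125,000)/0.014 = 600/0.014 = 42,857.

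- In A to C both versions pass against control and in-person gains more QALYs. Taking the most effective version that passes would choose in-person, although the step fails the threshold.
- In D, taking the lowest ratio against control would choose web, although the step to in-person passes ($40,000) and in-person has the higher NMB.
- The answer also depends on λ. In B at $100,000 per QALY, NMB is 100,000 × 0.010 − 100 = 900 for web and 100,000 × 0.015 − 500 = 1,000 for in-person, so the choice reverses.

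**The case against.** The strongest reply is that the head-to-head comparison is already planned. The statistical section says outcomes will be compared between the two versions, and the Abstract's Methods/Design lists economic measures among the outcomes. The word only does not appear in the economic section, and the clause promising cost per QALY and per BMI difference names no comparator. The model draws on all three arms, and the section commits to recommended practice for economic evaluation. A journal article may also leave ranking, dominance and acceptability curves to a fuller plan. Finally, both versions share one control arm, so in-person minus web follows by subtraction, and NMB against the common control ranks the options correctly. In Case A it picks web, as does the lower ratio.

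Much of this stands. A reader might infer that the protocol excludes an economic comparison of the two versions, or that its analysis will select the wrong one. The documents support neither inference: no exclusion is written, no decision rule is stated, and an error arises only if the ratios against controls are read separately.

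What the reply does not remove is the mismatch. Omitted detail could be left to another document, but here the protocol does state a comparator for incremental cost and for the model, and it is narrower than the protocol's own objective. Subtraction also yields only point estimates. The two contrasts share the control arm and are correlated, so the uncertainty of in-person minus web has to come from a joint analysis and cannot be read from two separate intervals.

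**Conclusion.** The point holds as a gap between objective and method. Objective 4 and both discussions require an in-person versus online cost-effectiveness result. The economic methods name controls as the comparator for incremental cost and for the model, and the general sentence on comparing outcomes is not carried into them. Under the hypothesised ordering, separate ratios against controls do not show whether in-person delivery justifies its additional cost over web.

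The size cannot be derived from the protocol. Across the assumed cases the step ratio runs from $40,000 to $200,000 per QALY, while the in-person ratio against control stays between $33,333 and $42,857. These figures show that misreading is possible, in either direction; they do not predict the trial's result. They assume positive QALY gains for both versions, web cheaper than in-person, and a $50,000 threshold. The design, the data collected and the primary clinical analysis are unaffected.

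**What to change.** Amend both economic subsections (Outcomes; Methods and analyses) so that the three arms are compared jointly:

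- Rank the options by cost and remove dominated ones.
- Report the in-person versus web incremental cost per QALY and per BMI unit, or the NMB of all three options over a range of thresholds.
- Take the uncertainty of that comparison from the probabilistic sensitivity analysis already planned, simulating all three arms together, for example as three-way acceptability curves.
- State that the conclusion on the preferred or optimal mode rests on this comparison. The versus-control ratios can stay as supporting results.

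The cost is a few sentences and some extra modelling output. No new data, visits or participants are needed.
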